### Sample size

The sample size has been calculated with NCSS-PASS software. At 5 years, peri-implant bone loss in metal-resin/metal-ceramic IFCDPs was 0.9 ± 0.4 mm and peri-implant bone loss in ceramic IFCDPs was 0.6 ± 0.1 mm [26]. In the proposed study, the criterion for significance is set at *α* = 0.05 (type I error) and *β* = 0.10 (type II error). The analysis is two-tailed. Assuming a dropout rate of 20%, in order to determine if there is a difference in the degree of bone loss between the two groups, 22 cases per group and 44 cases in total will be required. A previous study included 20 edentulous subjects who received two mandibular implants [10]. The abutments were either titanium or zirconium dioxide (non-submerged implant placement, within-subject comparison, left-right randomization). After 3 months, mean absolute counts of *Porphyromonas gingivalis* of the titanium vs. zirconia abutment were 1,000,000 ± 0 vs. 64,000 ± 36,770, respectively. However, the difference between groups was not evaluated in this study. Mean absolute counts (mean) for *Prevotella intermedia* of the titanium vs. zirconia abutment were 600,088 ± 952,117 vs. 3,600,089 ± 804,935, although the difference between the two groups was not evaluated. In this study, the criterion for significance will be set at *α* = 0.05 (type I error) and *β* = 0.10 (type II error). The analysis will be two-tailed. Assuming a dropout rate at 20%, in order to determine if there is a difference in the amounts of *P*. *gingivalis* and *P. intermedia* between the two groups, three patients per group and six patients in total will be required.

In summary, the total sample size will be 44 (22 per group).

### Statistical analysis

All statistical analyses will be conducted using IBM SPSS Statistics for Mac, version 19.0. (IBM Corporation, Armonk, NY, USA).

#### Clinical monitoring and X-ray assessment

Continuous variables will be described as the mean ± standard deviation or median. Grade and qualitative data will be described as a percentage. Age and other basic information between groups will be compared with the independent *t* test. Gender, implant survival rates, peri-implantitis rates, and peri-implant mucositis rates between the test and control groups will be compared using the chi-square test. PD and X-ray indices between groups will be compared using the independent *t* test. The differences in PLI and BI between the two groups will be evaluated, as well as the differences in PLI and BI over a period of 10 follow-ups. A generalized estimating equation will be used to eliminate possible internal correlations between multiple implants of the same patient. A Cox regression model will be used to exclude the influences of the shapes of the intaglio surface, the distances between the inserted implants, and other cofounders affecting the primary and secondary outcome variables. A probability (*p*) value of < 0.05 will be considered statistically significant.

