## Background

Full-arch fixed implant-supported prostheses have achieved satisfactory clinical results in edentulous patients with long-term implant survival of almost 100% [1]. However, biological complications after the placement of implant-supported fixed complete dental prostheses (IFCDPs) occur continuously over time [2]. Previous studies have indicated that peri-implant mucositis is associated with plaque accumulation [3, 4] around implants and prostheses and that the hygiene of IFCDPs could be influenced by the distance between the inserted implants in the jaw, the palatal extension of the prostheses [5], and the implant materials [6]. Investigations on the bacterial adhesion on titanium, the most commonly used materials in daily practice, have revealed that the corrosion of titanium increases plaque accumulation [7]. Zirconia ceramic frameworks, with or without ceramic veneering, is considered a promising material with good bio-compatibility and mechanical properties [8]. Therefore, many studies are currently investigating bacterial adhesion on zirconia discs/abutments as compared with titanium [9–12]. Results of in vitro studies suggest that zirconia is more resistant to bacterial colonization. However, in vivo evidence of bacterial control around implants remains controversial. For example, Grossner-Schreiber et al. [13] found that bacterial counts were higher with titanium discs than zirconia, while Scarano et al. [14] showed that bacterial adhesion was significantly higher with pure titanium surfaces as compared with zirconium oxide surfaces and Egawa et al. [15] found that bacterial adherence to titanium was comparable to that of zirconia if the surfaces of both materials had mirror-like flat textures.

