## Methods and study design

### Study design and setting

The proposed study is designed as a pragmatic randomized controlled trial with a 5-year follow-up period. A Consolidated Standards of Reporting Trials diagram is presented in Fig. 1. We plan to enroll 44 edentulous patients (mandible) in need of dental implant-based prostheses. The goal of the treatment protocol is to rehabilitate these patients with full-arch fixed implant-supported prostheses with placement of 4–6 titanium implants in the mandible. The patients will be randomly assigned to receive restorative materials of zirconia frameworks with ceramic veneering (Fig. 2) or titanium frameworks with acrylic resin veneering (Fig. 3). Both groups will receive titanium implants with sandblasted, large grid, and acid-etched surfaces. The trial will last for 5 years, and the patients will be followed up at 6-month intervals. During each visit, the patient will undergo a clinical examination, surface roughness test, and submucosa plaque collection, while biological and mechanical complications will be treated. One week before each visit, the patient will receive periodontal maintenance, including ultrasonic debridement using an ultrasonic device with polyetheretherketone-coated tips (AIRFLOW® Prophylaxis Master; EMS Dental, Nyon, Switzerland) combined with erythritol air-polishing (AIR-FLOW® handy 3.0 PERIO; EMS Dental). X-ray assessment will be performed yearly. A treatment timeline is shown in Table 1.

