### Primary and secondary outcome variables

The primary outcomes are the implant survival rate, PLI, peri-implant mucosal conditions, marginal bone resorption, and diversity of peri-implant submucosal bacteria species, while the secondary outcomes are the mechanical complication rate and surface roughness of the two treatment groups.

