### Randomization, allocation, and blinding

The subjects will be randomly allocated to one of two groups according to the prosthetic materials: titanium framework with acrylic resin veneering (group 1) or zirconia framework with/without ceramic veneering (group 2). The allocation of patients will be randomized using computer-generated permuted block randomization with an allocation ratio of 1:1. Randomization will be performed by sealed envelopes that will be opened after final impressions are obtained.

Microbiota analysis will be blinded after assignment to the intervention groups. Each sample will have a number associated with an allocation sequence, as well as information pertaining to the dental position and acquisition time. The technician conducting the PCR analysis will be blinded to the source of the sample. Interim statistical analysis will be performed at 1 and 3 years after implantation of the final prostheses. Final statistical analysis will be conducted at the end of the trial with the analyst blinded to both patient allocation and the interim analysis results.

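### Implant survival, a primary outcome expected near 100%, is compared between groups by chi-square on rates, which suits neither the few, clustered failures nor early dropout; the GEE and Cox models are not tied to that comparison.

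*Protocol article*

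**What the plan says.** All references are to the protocol article.

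- **Primary and secondary outcome variables** (the section so named) lists five: "The primary outcomes are the implant survival rate, PLI, peri-implant mucosal conditions, marginal bone resorption, and diversity of peri-implant submucosal bacteria species". Implant survival comes first in that list and is also named in the first aim under Objectives.
- **Clinical monitoring and X-ray assessment:** "Gender, implant survival rates, peri-implantitis rates, and peri-implant mucositis rates between the test and control groups will be compared using the chi-square test". The section names no exact test and does not say whether the unit is the implant or the patient.
- **Same section:** a GEE is planned to deal with correlation among implants in one patient; that sentence directly follows the one on PLI and BI. A Cox model is planned to remove the influence of confounders on the primary and secondary outcomes. Neither is named as the test of group difference in survival.
- **Background:** "long-term implant survival of almost 100" per cent is the cited experience with this type of restoration.
- **Study design and setting:** "placement of 4–6 titanium implants in the mandible", with visits every 6 months for 5 years.
- **Table 1:** implant survival is marked at months 12, 36 and 60 only.
- **Sample size:** 22 patients per group, derived for another outcome and with an assumed loss: "Assuming a dropout rate of 20%, in order to determine if there is a difference in the degree of bone loss between the two groups".

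**The concern.** A chi-square test on rates relies on enough expected events per cell, independent units, and a known status for each unit at the time point. The plan's own figures cast doubt on all three for implant survival. Failures will be few, several implants share one randomised patient, and about one patient in five is expected to leave before 5 years. A patient who leaves at month 48 with every implant in place must be either left out of the 5-year rate or counted as a 5-year success, and neither is right. At stake is whether the p-value and interval for a primary outcome can be taken at face value.

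**Working it through.** **Inputs.** From the protocol: 22 patients per arm, 4–6 implants per patient, 20% dropout, two-sided 5% level, 1:1 allocation by patient. Assumed: survival of 97–99% as a reading of the Background statement, and within-patient correlations of 0.1 and 0.3, since the protocol gives none. There is no planned power or event count for survival to reproduce, because the 22 per group was derived for bone loss.

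**1. Expected failures per arm** = implants per arm × (1 − survival).

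| Survival | 22 × 4 = 88 implants | 22 × 6 = 132 implants |
|---|---|---|
| 99% | 88 × 0.01 = 0.9 | 132 × 0.01 = 1.3 |
| 98% | 88 × 0.02 = 1.8 | 132 × 0.02 = 2.6 |
| 97% | 88 × 0.03 = 2.6 | 132 × 0.03 = 4.0 |

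All are below the customary minimum of 5, before any dropout. Five is reached only at a failure rate of 5/88 = 5.7% (4 implants each) or 5/132 = 3.8% (6 each). With the patient as unit, it is reached only if 5/22 = 22.7% of patients lose an implant.

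**2. True size of the implant-level chi-square** (no continuity correction, critical value 3.84, 22 × 5 = 110 implants per arm). Independent implants: exact binomial enumeration. Correlated implants: beta-binomial simulation.

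| Survival | Independent | Correlation 0.1 | Correlation 0.3 |
|---|---|---|---|
| 99% | 1.7% | 4.0% | about 9.4% |
| 98% | 4.2% | about 7.7% | about 15% |

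The low value at 99% is a matter of discreteness. For a failures against none, the statistic is (a/110)² / [p(1 − p) × 2/110] with p = a/220. It is 3.04 for 3 against 0 and 4.07 for 4 against 0. If one arm has no failures, the other must have at least four before the test can reject, while the expected count is 110 × 0.01 = 1.1.

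**3. Early leavers.** 44 × 0.20 = 8.8, so about 9 patients would have no 5-year status unless an implant failed before they left.

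**4. Do the other models settle it?** A hazard ratio or odds ratio for group is not finite if one arm has no failures. For 110 independent implants per arm, the chance that at least one arm has none is:

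- at 99% survival: 0.99^110 = 0.331, so 1 − (1 − 0.331)² = 55%;
- at 98% survival: 0.98^110 = 0.108, so 1 − (1 − 0.108)² = 20%.

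**5. What a better method can achieve.** At 98–99% survival the whole trial would see about 1.4 failed implants (completers only, 4 each, 99%: 2 × 70.4 × 0.01) to 5.3 (all patients, 6 each, 98%: 2 × 132 × 0.02). Taking five events and Schoenfeld's formula, power = Φ(½√5 × ln HR − 1.96). This gives Φ(0.775 − 1.96) = 12% for a hazard ratio of 2 and Φ(1.228 − 1.96) = 23% for 3.

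**The case against.** The best defence is that the same section already plans a GEE for implants within a patient and a Cox model for the primary outcomes. Clustering and censoring therefore both have a named method, and the section never says that the chi-square is run on implants. Part of this stands: the plan is not without tools for either problem. What it does not do is say which result is the group comparison of survival. Read as written, that is the chi-square, while Cox serves only to adjust for confounders, which a handful of failures could hardly support.

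Three stronger readings might be inferred, and the documents do not support them.

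- *That sparse cells inflate the false-positive rate.* With independent implants the test is conservative. Inflation comes only from clustering, whose strength is assumed here; at 99% survival and correlation 0.1 there is none.
- *That patients lost early cannot be used at all.* A failure seen before loss can be counted, and late leavers contribute to the 12-month and, if still present, the 36-month rates.
- *That Cox and GEE are useless here.* Only the ratio estimate fails when one arm has no failures. The score test from a Cox model with group as the only covariate is the log-rank test and stays defined.

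The defence is also right that a change of test adds almost no power, and that the Background figure is not a planning value. At 96% survival with six implants each, the expected count is 132 × 0.04 = 5.3, above 5.

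**Conclusion.** The point holds as a mismatch between the named test and the data the plan expects. At 97–99% survival, expected failures per arm are about 0.9–4.0. At 98–99% survival, the true level of a nominal 5% implant-level test could lie anywhere from about 1.7% to 15%, depending on survival and clustering. The direction of error is therefore not known in advance. The upper part of that range rests on assumed correlations and on the chi-square being applied to implants without adjustment. The censoring problem is confined to the long-term rates and to about 9 of 44 patients. The sparse-count result is for survival only; peri-implantitis and mucositis share the sentence, and for them the point is just that the plan should say whether the GEE replaces the chi-square.

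**What to change.** In the section on clinical monitoring and X-ray assessment:

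1. Replace the chi-square for implant survival with time to first implant loss per patient: Kaplan–Meier curves censored at the last visit, compared by an exact or permutation log-rank test. Report patient-level survival by arm with a confidence interval.
2. State that the GEE already planned, with patient as the cluster, replaces the chi-square for implant-level peri-implantitis and mucositis rates, or that a patient-level exact test does so if events are few.

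The design and sample size do not change. There is a small data cost: the date or visit interval of each loss must be recorded at the 6-monthly visits, because Table 1 marks survival at three time points only. The write-up should also say plainly that the survival comparison will be valid but have little power, so the interval matters more than the p-value.

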### X-ray assessment

Marginal bone loss (MBL): immediately after placement of the final prosthesis, a periapical radiograph of each implant will be obtained as well as every year afterward. For standardization, a paralleling technique will be conducted using an intramural digital system (Digora Toto, Soredex, Tuusula, Finland). Kodak Dental Imaging 6.1 software (Carestream Health, Inc., Rochester, NY, USA) will be used for radiographic analysis. The crestal bone level will be measured as the vertical distance between 2 mm below the implant–abutment interface and the most crestal part of the alveolar bone [23, 24]. MBL will be measured mesially and distally for each implant. In each group, peri-implant MBL will be measured to the nearest millimeter.

A peri-implantitis lesion is defined as having PD of ≥ 5 mm with positive suppuration or BI of ≥ 1 and radiographic evidence of bone loss (> 2 mm) or according to consensus [25]. Peri-implant mucositis is defined as being positive for suppuration or BI of ≥ 1 with no radiographic evidence of bone loss. A healthy implant site is defined as a PD of ≤ 4 mm, BI = 0, and no radiographic evidence of bone loss.

The incidences of peri-implantitis and peri-implant mucositis will be determined at 1, 3, and 5 years after final restoration.

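### Confounder adjustment is assigned to a Cox model that most of the outcomes cannot enter, and the role of the GEE beside the named t and chi-square tests is not fixed

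*Protocol article*

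**What the plan says.** The section that defines the outcomes reads: "The primary outcomes are the implant survival rate, PLI, peri-implant mucosal conditions, marginal bone resorption, and diversity of peri-implant submucosal bacteria species". The secondary outcomes are mechanical complications and surface roughness.

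The section on clinical monitoring and X-ray assessment (under Statistical analysis) then sets out the following.

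- Rates: "Gender, implant survival rates, peri-implantitis rates, and peri-implant mucositis rates between the test and control groups will be compared using the chi-square test".
- Probing depth and bone: "PD and X-ray indices between groups will be compared using the independent" t test.
- Plaque and bleeding indices: differences between groups and over the ten follow-ups are to be evaluated; no test is named.
- Clustering: one sentence says that a GEE will deal with correlation among implants in the same mouth. It is not tied to particular outcomes.
- Confounders: "A Cox regression model will be used to exclude the influences of the shapes of the intaglio surface, the distances between the inserted implants", extended to other "cofounders affecting the primary and secondary outcome variables".

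The next section, on surface roughness, names an independent t test and mentions no GEE. The microbiological section averages species counts within each subject before groups are compared.

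On timing, the X-ray assessment section says: "The incidences of peri-implantitis and peri-implant mucositis will be determined at 1, 3, and 5 years after final restoration". Allocation uses "sealed envelopes that will be opened after final impressions are obtained".

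**The concern.** A Cox model needs, for each unit, a time and an indicator of event or censoring. The plan points it at the primary and secondary outcomes without distinction, and most of these have neither. The adjusted analysis therefore has no executable form for most outcomes, and someone would have to choose a substitute after data have accrued, possibly at the 1-year or 3-year interim analysis.

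The GEE sentence leaves a second gap. Each patient has 4 to 6 implants. The tests named for probing depth, bone and disease rates assume independent observations, and the text does not say whether they are run on implants or patients, or whether the GEE supersedes them. Two analysts could follow the text faithfully and report different p-values.

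There is also a smaller question about one covariate. Because the envelopes are opened after impressions, the fitting-surface (intaglio) shape may be settled once the material is known. Adjusting for it could then remove part of the effect under study.

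**Working it through.** **1. Can each outcome enter a Cox model?**

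| Outcome | Form in the Protocol article | Group test named | Event time? |
|---|---|---|---|
| Implant survival | rate, Table 1 at Months 12, 36, 60 | chi-square | none defined; could be built |
| Plaque index | score 0–3 | none named | no |
| Bleeding index | score 0–4 | none named | no |
| Probing depth | millimetres | t test | no |
| Peri-implantitis, mucositis | incidence at 1, 3, 5 years | chi-square | none defined; could be built |
| Marginal bone loss | millimetres | t test | no |
| Diversity | Shannon, Margalef, Pielou indices | t test | no |
| Mechanical complications | four grades per visit | none named | none defined; could be built |
| Surface roughness | profilometer reading | t test | no |

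Six of the nine rows cannot enter a Cox model. The other three could, but the plan defines no event time for any of them and compares survival and disease as rates. The Background describes long-term implant survival as close to 100%, so a Cox model for implant loss would have few events.

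**2. What is at stake in the open role of the GEE?**

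The plan gives no figure to reproduce here. Inputs:

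- implants per patient m = 4 to 6 (Interventions); 5 taken as the middle
- two-sided nominal 5% level (Sample size)
- about 18 evaluable patients per arm: 22 × (1 − 0.20) = 17.6
- intra-patient correlation (ICC) 0.1, 0.3, 0.5: an assumed range, since the document gives none

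Design effect: DE = 1 + (m − 1) × ICC. True level of a test that treats implants as independent: 2 × [1 − Φ(1.96/√DE)].

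For m = 5:

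- ICC 0.1: DE = 1 + 4 × 0.1 = 1.4, level 0.098
- ICC 0.3: DE = 1 + 4 × 0.3 = 2.2, level 0.186
- ICC 0.5: DE = 1 + 4 × 0.5 = 3.0, level 0.258

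Simulation with 18 patients per arm and 5 implants each gave 0.102, 0.192 and 0.258. By formula, the levels at the same three ICCs are 0.086, 0.155 and 0.215 with 4 implants, and 0.110, 0.215 and 0.295 with 6.

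On the other reading, a t test on patient-level values held its level in simulation (0.048 to 0.051). A GEE with an uncorrected sandwich z test ran at about 6.3% to 6.7% with 18 clusters per arm, which is why a small-sample correction belongs in the wording.

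**3. Roughness.** Readings are taken at six points per abutment and each is repeated. With 5 implants that is 5 × 6 = 30 points per patient before repeats. The section names only a t test and states no averaging step.

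**4. Covariates and the time of allocation.** Table 1 puts implant surgery (T1) and impressions (T2) before allocation (Month 0). Implant number and inter-implant distance are thus fixed before allocation. Allocation and final restoration are both at Month 0, so the prosthesis shape may be fixed afterwards. No passage says that shape differs by material.

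**The case against.** The strongest reply concerns clustering. A reader might infer that the plan ignores the correlation between implants. It does not: the GEE sentence stands immediately before the Cox sentence, closes the list of clinical and X-ray comparisons, and is not limited to the plaque and bleeding indices. Species counts are averaged per subject. This stands. The 10% to 26% therefore describes an uncorrected implant-level analysis that the plan leaves open but does not commit to, at assumed correlations. What remains is that the GEE's role is not fixed and that roughness has no stated cluster handling.

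Four other stronger readings also fail.

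- **Month 0 values are wrongly left out.** No named test uses them as a covariate, but in a randomised trial that costs precision, not validity, and a condensed article may leave covariates to the analysis plan. Bone loss already implies a comparison with the film taken at placement. At assumed correlations of 0.3 and 0.5 with follow-up, adjustment leaves 1 − 0.09 = 0.91 and 1 − 0.25 = 0.75 of the variance.
- **The t test is invalid because the planning SDs differ (0.4 and 0.1 mm).** The section does not specify the equal-variance form. Even that form runs near 5.6% at 18 per arm. Levels of 9% or 12% need lopsided loss (15 versus 20, or 14 versus 22) with the high-SD arm the smaller; reversed, they are about 3% and 2%.
- **Adjusting for intaglio shape removes a treatment effect.** The design allows this; nothing in the document shows it.
- **Cox has no place here.** Implant loss, peri-implantitis, mucositis and mechanical complications could be given event times.

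It could also be said that the analysis plan will settle the models. That answers an omission. The Cox sentence is a stated method that does not fit the outcomes to which it is assigned.

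**Conclusion.** The point holds in limited form. The Cox adjustment as stated cannot be run for plaque index, bleeding index, probing depth, marginal bone loss, diversity or roughness. This rests on the outcome definitions alone and needs no assumption.

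The clustering part is an ambiguity, not an omission. Its potential size is a true error of about 10% to 26% in place of 5%, conditional on three things: tests run on implants as independent units, 5 implants per patient, and an ICC between 0.1 and 0.5. If the GEE or patient-level values are used, the inflation is largely or wholly avoided.

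The unadjusted comparison of the randomised groups does not depend on the Cox model, so the trial's main contrasts are not undermined. This should be fixed before the 1-year interim analysis; it does not put the trial in doubt.

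**What to change.** 1. For each implant-level outcome, name one between-group test that accounts for the patient: a GEE with a small-sample correction, or a linear mixed model for continuous outcomes, including bone loss and roughness. Say that it replaces the t and chi-square tests now listed for those outcomes.
2. Put the pre-allocation covariates, implant number and inter-implant distance, in that model and delete the general Cox sentence. For diversity, the same covariates can enter a linear model for the index.
3. Restrict Cox regression, with patient-clustered standard errors, to time to implant loss or time to complication, with the event and its time defined. If events are few, use an exact patient-level test.
4. Keep intaglio shape to a sensitivity analysis.
5. Optionally, add the Month 0 value for probing depth, plaque index and bleeding index as a gain in precision.

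The cost is wording and slightly more analysis work. The listed covariates and the Month 0 values are already recorded. Confidence intervals will be wider than from an implant-level test, and correctly so.
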